#### Quantitative data

Data will be collected in relation to the number of patients approached, who agree to participate in the trial, and who are randomised. The number of best usual care sessions run and the number of attendees at each session will be recorded.

#### Participant interviews

A purposive sample of patient participants will be interviewed once they have completed their 3-month follow-up questionnaire. In choosing to do these interviews at this time we are mindful that the interviews themselves might introduce bias into our between-group comparison and that there will be some loss in quality of the qualitative data because of recall bias. Pragmatically, we will do these after we have collected 3 months of follow-up needed for our primary analysis. Interviews will be face to face or by telephone. The choice will be left to the participant to help maximise recruitment. We will recruit for diversity of age, gender and baseline severity of back pain. Interviews will be audio recorded and transcribed. Early interviews will be reviewed and the interview schedule developed based on the data. Recruitment will continue until data saturation. We expect this to be after approximately 15 interviews.

Interviews will cover: past experience of back pain, actions taken to help back pain such as treatments sought, how the participant summarised their experience of back pain as a diary pain score and in response to the EQ-5D-5 L, expectations of the effect of the intervention and whether these were met, any change the participant thinks that has or has not occurred, and experience of trial processes such as recruitment process and use of the diary.

#### Focus groups/interviews with trial team members and clinicians delivering intervention

We will run focus groups (or, if impractical, interviews) with trial team members involved in recruitment and data collection and with clinicians delivering interventions and clinic staff associated with intervention delivery. We will undertake this data collection at each recruiting Trust. Focus groups will be facilitated by an experienced researcher. Where possible they will be observed by a second researcher. Focus groups and interviews will be audio recorded. The topic guide will include: experience of patient recruitment and assessment, intervention delivery, and outcome data collection.

#### Observation of assessment at trial entry and delivery of intervention/control intervention

A researcher independent of the team will sequentially observe up to five of each of: initial assessment, intervention, and control intervention events. The researcher will take field notes and provide almost immediate feedback to the trial team on issues of variation in delivery so these can receive attention. The observations will then inform the development of quality control criteria. The trial team will review and refine draft criteria, which will then be tested on a further five events of each type later in the trial.

### Analysis

We will develop a detailed statistical analysis plan prior to any analyses. Summary statistics will be generated for all variables and data will be presented in tables and charts as appropriate.

The main quantitative outputs from this feasibility trial will, first, be process outcomes assessed for the whole trial population rather than for each treatment group separately and will include:Proportion of eligible participants who are randomised and complete follow-up;Proportion who obtain immediate (diagnostic) pain relief;Recruitment rates; number of referrals per site and proportion of referrals converted to participants. These data are needed to estimate number of sites needed for, and duration of, the main trial;Completeness of data from short-term electronic data collection.

Between-group comparisons will be conducted on an intention-to-treat basis, with all participants considered to be in the facet joint injection group if they are randomised to that group even if injections are contra-indicated. We will also perform between-group comparisons of the following outcomes on an intention-to-treat basis:Average pain, as measured using text messaging (or paper back-up), over 3 months;

ANDBack pain-related disability, as measured using Roland Morris disability questionnaire (RMDQ), reported at 3-month follow-up.

If it is not feasible to recruit sufficient participants to make these between-group analyses meaningful they will omitted.

We will adjust our models for baseline stratification factors and other baseline covariates.

#### Analysis of qualitative data

The objectives of the process evaluation will provide the framework for analysis of the interview transcripts, observation field notes and focus group transcripts. We will undertake a thematic analysis, interrogating and coding the data for each of the objectives. Data relevant to each theme will be compared within samples (patients/observed events/focus groups) paying particular attention to variation in the data from participants with different characteristics (e.g. age) or from different contexts. Data relevant to each theme will also be compared across samples e.g. contrasting patient/clinician data. The analysis will be written up as a report to inform the design of a subsequent main trial.

Data will be synthesised and anonymous quotations will be used as exemplars of themes.

### Regulatory authorities/ethical approval

The Facet Injection Study comes under the definition of a Clinical Trial of an Investigational Medicinal Product (CTIMP) under the EU Clinical Trials Directive 2001/20/EC and will therefore require submission to the Medicines and Healthcare Products Regulatory Agency (MHRA). In accordance with ICH E6-GCP ethical approval was obtained on 20 August 2014 (Committee Yorkshire and the Humber – Sheffield, REGO 2013-592). MHRA approval was obtained on 18 November 2014 (ref. 13268/0001/001-0001, Eudract number: 2014-000682-50).

### Investigational medicinal product (IMP)

A study ‘injection manual’ will be prepared to ensure that all sites adhere to the same procedures when delivering the facet joint injection.

The IMP 1 ml of levobupivacaine 5.0 mg/ml and 1 ml of triamcinolone 10 mg/ml prepared within the same syringe will be used for each facet joint injection procedure. Preparation of the injection will be undertaken by the operator immediately prior to the injection. A total volume of 2 ml will be injected through the spinal needle placed into each joint (see Fig. 2). This approach of mixing such drugs immediately prior to facet joint injection is standard practice for this procedure within the NHS.

### Drug storage and dispensing and drug accountability

The IMP used will be the usual drug provided for use by the participating Trust’s pharmacy departments. Appropriate procedures will be established and monitored to ensure that the drugs are correctly stored, dispensed and accounted for. The study team will adhere to appropriate standard operating procedures and legislation for trials of IMPs.

### Adverse event management

Adverse events will be managed in line with Warwick CTU’s standard operating procedures

### Adverse events (AEs)

We expect that participants will experience some uncomfortable effects from participation in the ‘best usual care’ treatment – for example muscle or joint soreness in response to exercise, feeling unwell or anxious. These and similar effects are entirely to be anticipated, and provided they are short-lived or dealt with through clinical management should not be reported as adverse events.

The following are expected adverse events and will be recorded in the case report form (CRF):Pain, bleeding, discomfort and minor bruising at the injection site (transient)Numbness in the buttocks and legs from local anaesthetic (transient)Infection of injection site (uncommon)Inadvertent intravenous injection (uncommon)Musculoskeletal injuries requiring medical attention including serious sprains, joint dislocation, falls or other injuries occurring as a direct consequence of the intervention (i.e. whilst participating in the ‘best usual care’ physiotherapy treatment intervention in real-time) should also be recorded.

All serious adverse events (SAEs) and suspected unexpected serious adverse events (SUSARs) that occur between trial entry and up to the end of the final ‘best usual care’ physiotherapy treatment session will be entered onto the SAE reporting form within the participant’s CRF. Reporting of SAEs and SUSARs will follow Warwick Clinical Trials Unit’s standard operating procedures and legislation.

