### Facet joint injections (visit C)

For those participants who are randomised to undergo facet joint injection the injection will take place between the first and second best usual care sessions. The treating clinician will at this time make their own assessment of the participant’s suitability for facet joint injection and obtain consent for the procedure following normal practice in each participating Trust. The treating clinician may postpone injection in the presence of short-term illness (e.g. influenza). If significant comorbidity is identified at this time that contra-indicates injection, this will be ‘flagged’ to the patient notes, local investigator, site clinician or general practitioner, whichever is most appropriate. The participant will continue to receive the control intervention.

Up to six facet joints (L3/L4, L4/L5, L5/S1 bilaterally) in each participant will be injected. However, where, on clinical assessment, there is unilateral pain, or involvement of only some levels, the operator may choose to do unilateral injection, or be selective on levels injected. This pragmatic approach reflects current clinical practice within the NHS.

Figure 2 outlines the injection procedure that was agreed at consensus [4].

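### The exemption of physiotherapy effects from adverse event reporting can leave non-specific, non-serious effects of the injection unrecorded, because it turns on an attribution for which the article gives no rule

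*Protocol article*

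**What the plan says.** All of this is in the protocol article.

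- **Adverse events (AEs), the exemption.** It opens with the cause it covers: "We expect that participants will experience some uncomfortable effects from participation in the" best usual care treatment. Its examples are "muscle or joint soreness in response to exercise, feeling unwell or anxious". It is then left open-ended: "These and similar effects are entirely to be anticipated". The instruction to sites is that these effects, "provided they are short-lived or dealt with through clinical management should not be reported as adverse events".
- **Adverse events (AEs), the recording list.** Expected adverse events go in the case report form. The first two items are "Pain, bleeding, discomfort and minor bruising at the injection site (transient") and "Numbness in the buttocks and legs from local anaesthetic (transient"). The others are injection-site infection, inadvertent intravenous injection, and musculoskeletal injuries that need medical attention and arise directly from the intervention.
- **Adverse events (AEs), serious events.** All SAEs and SUSARs from trial entry to the last physiotherapy session are entered.
- **Facet joint injections (visit C).** In the intervention arm, "the injection will take place between the first and second best usual care sessions".
- **Adverse event management.** Adverse events are handled under the trials unit's standard operating procedures, which are not shown.

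**The concern.** The exemption is defined by cause, but several of the symptoms it names do not reveal their cause. Feeling unwell or anxious is non-specific. Soreness in the lower back is ambiguous in someone who is exercising and has also had lumbar joints injected. The article describes no sham injection and no blinding, and participants are told whether they need to attend for an injection. Whether such a symptom reaches the adverse event record therefore depends on an unblinded judgement made before anything is written down. An event judged to be a physiotherapy effect leaves no adverse event entry that could be re-examined later.

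At stake is the quality of the non-serious harm data. The trial is a CTIMP, it has no Data Monitoring and Ethics Committee, one of its objectives is to test the injection protocol, and its data feed a decision model that includes health consequences. The four listed injection effects can arise only in people who are injected. Non-specific symptoms are the non-serious effects that could be compared between arms, and they are the ones the exemption names.

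**Working it through.** The plan states no figure on this point, so the check sets the rules against the treatment sequence.

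**1. Do the exposures overlap in time?** Everyone has a first physiotherapy session and is then randomised. The injection follows within 3 weeks of randomisation and before the second session. All sessions end within 12 weeks of randomisation. An injected participant therefore has physiotherapy before and after the injection, and a symptom in the days after it can follow both exposures.

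**2. Which rule catches which symptom in an injected participant?**

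| Symptom after injection | Recording list | Exemption | Outcome |
|---|---|---|---|
| Pain, bleeding or bruising at the injection site | Named | Does not apply (wrong cause) | Recorded |
| Numbness from the anaesthetic | Named | Does not apply | Recorded |
| Injection-site infection, intravenous injection | Named | Does not apply | Recorded |
| Any serious event | SAE/SUSAR rule | Does not displace that rule | Recorded |
| Lumbar soreness, source unclear | Only if judged to be injection-site pain | Applies if judged to be exercise soreness | Depends on attribution |
| Feeling unwell or anxious | Not named | Applies if judged to be a physiotherapy effect | Depends on attribution |
| Other general symptoms | Not named | May fall under the open-ended extension | Depends on attribution |

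The first four rows are secure. The last three turn on attribution, and the article gives no rule for it.

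**3. How wide is the exemption?** Its two conditions are joined by *or*. An effect that is not short-lived is still exempt if it is dealt with clinically, so brevity alone does not bound what is left out.

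**4. Can the loss be sized?** Let *p* be the proportion of injected participants with a non-specific symptom caused by the injection, and *m* the proportion of those symptoms attributed to physiotherapy. Unreported events = 75 × *p* × *m*. The documents give neither *p* nor *m*. With *p* = 0.10, purely as an assumption, there are 75 × 0.10 = 7.5 such events, and the number unreported is:

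- *m* = 0: 0
- *m* = 0.5: 7.5 × 0.5 = 3.75
- *m* = 1: 7.5

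The answer runs from none to all of the events according to the assumed *m*. This shows the mechanism and does not estimate its size.

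**The case against.** The strongest reply is that the exemption is limited to effects of best usual care, so effects of the injection fall outside it as written. This stands against one tempting inference, that the rule contradicts the instruction to record transient injection pain. The exemption is bounded by cause, and the listed items by the injection site, the anaesthetic or the procedure, so a site can follow both. It does not remove the difficulty, because applying the exemption requires the cause to be known.

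Second, site and timing separate many events. Injection-site pain, bruising and numbness are identifiable, the injection has its own visit, and pain is scored 45–60 minutes before and after it. A reader might infer that drug and physiotherapy effects cannot be told apart at all. That goes too far: the ambiguity is confined to non-specific symptoms and lumbar soreness.

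Third, this is a condensed article that refers adverse event management to standard operating procedures, and the list of expected events is not said to be exhaustive. It would be wrong to conclude that no place exists for an unlisted systemic reaction. But the point rests on an instruction the article does give, and nothing shown says that the general procedures override it.

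Fourth, daily then weekly pain scores in both arms and repeated EQ-5D-5L would show a marked short-term worsening. That is fair, but these scores do not record what the symptom was.

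Fifth, no stated objective is to estimate the between-arm excess of non-serious events, and 75 injected participants would give an imprecise estimate. That limits the weight of the point. It does not justify leaving the recording to an unguided attribution.

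**Conclusion.** The point holds as a risk of incomplete recording. Short-lived or clinically managed non-specific symptoms after the injection can be put down to physiotherapy without blinding and go unreported, so non-serious injection effects can be under-counted. A reader might go further and conclude that injection harm *is* under-counted. The documents do not establish that: they give no event or misattribution rates, the listed local effects are recorded, and SAEs and SUSARs are entered throughout the stated window. The amount cannot be estimated from the article; the people exposed to the problem are the 75 planned for the injection arm.

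The conclusion rests on two assumptions: that sites apply the exemption as the article words it, and that the unseen operating procedures do not narrow it for injected participants. If they do, the article's wording need only be brought into line with them. The consequence is modest, but the change is cheap and worth making.

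**What to change.** Amend the adverse event section and the case report form as follows.

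1. State that the exemption does not apply to new symptoms that start on or after the injection and within a fixed window, with its length specified in advance.
2. Record these symptoms in the case report form with their onset date, whatever the suspected cause. A view on cause can be noted beside the entry but should not decide whether it is made.
3. Ask control participants about the same symptoms, at their existing physiotherapy sessions, over a comparable window. As the injection is due within 3 weeks of randomisation, the control window can be anchored to randomisation.

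The cost is revised form wording, a short instruction to sites, and more non-serious event entries in both arms, many of which will be ordinary exercise soreness. No extra visits are needed. The article describes recruitment as being in its early stages, so the date of the change should be noted, since participants treated before it will have been recorded under the present rule. This concerns recording only and changes no clinical management.

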### Outcome measures

Table 1 below summarises the outcome measures and their time of completion by participants. The main questionnaire packages are completed at baseline (at trial entry assessment) and follow-up (3, 6 and 12 months post randomisation). A pain severity (today) score will be recorded daily for 35 days from 7 days before the first treatment session and following this weekly until 3-month follow-up. For this we are testing the use of text messaging to allow participants to respond by text. However, paper diaries will be provided as a back-up as this is our primary outcome. Health utilities (measured using the EuroQol EQ-5D-5 L) will be recorded weekly from 1 week prior to the first treatment session until the night before the injection appointment when we will ask participants to complete the EQ-5D-5 L measure for 8 days then weekly until the 3-month follow-up. In addition, intervention participants will record a pain severity score 45–60 minutes before and after injection. Clinical data will be collected and recorded by physiotherapists and clinicians, covering patients’ assessments, injections and involvement in the best usual care. It may be necessary to increase the number of data points for the EQ-5D-5 L and the pain severity score; first, if an injection is cancelled/rescheduled and second, towards the end to ensure test-retest reliability. We will undertake postal follow-up with two postal reminders, and one telephone call for primary outcomes at 3, 6 and 12 months.

**Table 1 Tab1:** Outcome measures and delivery time points

Type of data	Outcome measures	Time points				
		1^a^	2^b^	3^c^	4^d^	5^e^
Demographic	Age, gender, ethnic group, age at leaving full-time education, occupation, current work status	Yes				
History	Time since completely free of back pain	Yes				
History	Previous back pain treatments	Yes				
Medications	Current medications	Yes				Yes
History	Satisfaction with health state	Yes				Yes
History	Troublesomeness question	Yes				Yes
Back pain-related disability	Roland Morris disability questionnaire [14]	Yes				Yes
Back pain-related disability	The modified von Korff (MVK) disability score. [15, 16]	Yes				Yes
Back pain severity	MVK pain scale [15]	Yes				Yes
	Modified form of Patient-Generated Index [17, 18]	Yes				Yes
Psychological distress	Depression, Anxiety, and Positive Outlook Scale (DAPOS). [19]	Yes				Yes
Pain self-efficacy	Pain self-efficacy questionnaire [20]	Yes				Yes

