Health-related quality of life	SF-12 version 2, reported as physical and mental component scores [21]	Yes				Yes
Health utilities	EuroQol EQ-5D-5 L [22, 23]	Yes		Yes	Yes	Yes
Well-being	Warwick-Edinburgh Mental Well-being Scale (WEMWEBS) [24]	Yes				Yes
Pain distribution	Troublesomeness grid [10]	Yes				
Back pain severity today	11-point pain rating scale [16]		Yes	Yes		
Current work status	If appropriate date of return to work					Yes
Health and social service resource use	Including hospital and community resource, as well as costs to individuals and carers					Yes

^a^1. Baseline - following clinical assessment

^b^2. Intervention only, day of injection 45–60 minutes before and after injection

^c^3. Daily pain score for a period of 35 days starting 7 days before first physiotherapy treatment (via SMS) after which weekly until the endpoint (3 months)

^d^4. EQ-5D-5 L weekly from first physiotherapy treatment session until night before injection appointment when daily for 8 days; then back to weekly until the endpoint (3 months)

^e^5. Follow-up – 3, 6 and 12 months post randomisation

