### First ‘best usual care’ session (visit B1)

All participants will be scheduled a first 1-hour session with a study-trained physiotherapist. Treatment will follow guidance from NICE [2, 3], but tailored to individual patients. Participants will undergo a thorough initial physical assessment (60 minutes) based on the principles of Maitland manual therapy [13]. The assessment will also include discussion of patient expectations, fear avoidance and perceived self-efficacy.

Once the first trial physiotherapy session is completed, the participant will be randomised to receive facet joint injection with the best usual care package (intervention arm), or the best usual care package only (control arm). The investigator trial team will then complete the randomisation process and inform the participant whether they need to attend for an injection. This will take place within 3 weeks of randomisation.

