### ‘Best usual care package’ (visits B2 to B6)

The five remaining sessions will last approximately 30 minutes. All participants (those in the intervention and those in the control arms) will be encouraged to attend all of these sessions. The package is one-to-one sessions with a study physiotherapist who will use the best usual care manual informed by consensus [4]. Sessions will be a bespoke package of physical and behavioural rehabilitation.

All treatment sessions will be complete within 12 weeks of randomisation.

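### SAE and SUSAR entry ends at each participant's final physiotherapy session, so time under observation after the injection has no fixed end or minimum and depends on attendance

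*Protocol article*

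**What the plan says.** The Adverse events section of the Protocol article requires SAEs and SUSARs "that occur between trial entry and up to the end of the final ‘best usual care’ physiotherapy treatment session will be entered" on the SAE form in the case report form. The same section leaves the reporting procedure to the trials unit's standard operating procedures and to legislation.

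The visit sequence is set out in four other places:

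- First session (visit B1): "Once the first trial physiotherapy session is completed, the participant will be randomised". On the injection appointment, the same section says "This will take place within 3 weeks of randomisation".
- Facet joint injections (visit C): "the injection will take place between the first and second best usual care sessions". The clinician may postpone it for short-term illness.
- Best usual care package (visits B2 to B6): participants in both arms "will be encouraged to attend all of these sessions", and "All treatment sessions will be complete within 12 weeks of randomisation".
- Outcome measures: questionnaires at baseline and "follow-up (3, 6 and 12 months post randomisation"). Pain scores are collected daily and then weekly to 3 months. Table 1 as shown has no adverse event item; the nearest is resource use, described as "Including hospital and community resource, as well as costs to individuals and carers".

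**The concern.** A safety window would ordinarily be set by time from randomisation or from exposure. Here its end is an attendance event that happens after randomisation, and the exposure of interest, the injection, comes after the first of six sessions. How long a participant is observed for serious events after injection therefore depends on how far they go with physiotherapy.

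The article gives reasons to expect the treatment to influence this. The Abstract hypothesises that injection helps people engage with physiotherapy, and the Background names continuing or increasing pain as a barrier to engagement. If injection helps, injected participants may attend for longer and be observed for longer. If it leads to more pain, they may stop sooner and be observed for less time. The direction cannot be known in advance.

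At stake are the completeness of serious event capture after a medicinal product is given, the meaning of any table of serious events by arm, and the safety procedure that a main trial would inherit from this feasibility study.

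**Working it through.** The plan gives no figure for the length of the safety window, so there is none to reproduce. The length follows from the visit timeline.

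**Inputs** (Protocol article)

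- Randomisation follows completion of B1; take this as week 0.
- Injection week *i* lies between 0 and 3 (First session, visit B1).
- The final session is in week *s*, at the latest week 12 (visits B2 to B6).
- Injection precedes B2 (visit C).

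**Formula**

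Time observed for SAEs after injection = *s* − *i*, or zero if the final session precedes the injection.

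**Results**

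| Participant | Calculation | Time observed after injection |
|---|---|---|
| Final session week 12, injected at week 3 | 12 − 3 | 9 weeks |
| Final session week 12, injected at about week 0 | 12 − 0 | 12 weeks |
| Final session before week 12 | *s* − *i* | one week less for each week earlier |
| Stops after B2, final = last attended | B2 − *i* | injection to B2 only; spacing not given |
| Injected, never returns, final = last attended | B1 precedes injection | 0 |

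The 12-week rule is an upper limit, so the third row applies to participants who comply fully but finish early. It holds under either meaning of the final session. The last two rows depend on the attendance meaning.

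Under that meaning the gap is not confined to the injection arm. Because randomisation follows B1, a control participant who does not return also has a window that closes before any time after randomisation has been observed.

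**Comparison with a time-based end.** A window closing 12 weeks after randomisation gives everyone injected within the 3-week limit at least 12 − 3 = 9 weeks, whatever their attendance. A postponement beyond week 3 would reduce this, as it would under the present rule.

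**Other sources of safety data.** Expected adverse events are recorded in the case report form with no stated end date. Pain scores run to 3 months and resource use is asked at each follow-up. None of these is a systematic enquiry about serious events, although resource use might reveal a hospital contact.

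**The case against.** The strongest reply is that the final session means the last of a fixed sequence of six, so that a participant who drops out stays under observation until the planned date of B6. That is a reasonable reading, and under it the zero-window case disappears. The text does not state it, however, and gives no end date for someone whose later sessions are never booked. Even on this reading the window has no fixed length.

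A second reply is that this is a condensed article and the operating procedures or legislation may require more. They may. But the article states the cut-off itself and refers to those sources for reporting, so this is a rule open to comment and not an omitted detail.

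Several stronger inferences are tempting and are not supported:

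- **That injected participants who drop out have no safety follow-up.** This is true at most of SAE and SUSAR entry, and only under the attendance reading. The other data described above are still collected.
- **That the planned analysis is biased.** The Analysis section lists two between-group comparisons, average pain and Roland Morris disability. No comparison of SAEs is planned.
- **That the arms have different session timetables.** Both have the same six sessions and the same 12-week limit. Any difference would come through attendance, which the article suggests but does not quantify.
- **That a particular number of injected people would be missed.** The article gives no rate of non-return. Its 20% allowance concerns loss to outcome follow-up, not physiotherapy attendance.
- **That oversight was neglected because there is no data monitoring committee.** The funder agreed to this and appointed an independent Trial Steering Committee.

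**Conclusion.** The point holds as a badly fixed rule: the end of SAE and SUSAR entry is set by physiotherapy attendance or scheduling and not by time. Time observed after injection is 9 to 12 weeks when the final session is at week 12 and shorter for those who finish earlier. Under one of the two possible meanings of the final session, it is nothing for an injected participant who does not return. The 9-to-12-week range assumes that the 3-week limit on the injection is kept.

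A count of SAEs by arm could rest on unequal observation time if attendance differs between arms. The article's own rationale makes that plausible but gives neither size nor direction. With no formal SAE comparison planned and other safety-related data collected, this should be corrected but does not threaten the trial's stated comparisons.

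**What to change.** In the Adverse events section, replace the final-session cut-off with an end defined by time from randomisation, the same in both arms and independent of attendance. The existing 3-month follow-up is a natural choice. Add a question on serious events to that contact for all participants, including those who have stopped physiotherapy; the postal questionnaire, reminders and telephone call are already planned. When SAEs are tabulated by arm, state the common window.

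The cost is a sentence in the protocol, one question at an existing contact, and a few more SAE forms to process. The article describes recruitment as at an early stage, so the change could still cover most participants.
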